### Social Support

The Physical Activity Social Support Scale [25] will be given to all students in Stage 3 (years 5 and 6) classes as a survey, and used to collect self-report data measuring sources of adult and peer support of physical activity. Test-retest reliability of the scale is strong (ICC = .88) and the Internal consistency of the items was evaluated at α = .77 [26]. The tool is a 15 min survey with nine questions about how often students receive encouragement to be physically active and from who. The response to each question is divided into adult male, adult female and other children (peers), and anchored to a six-point Likert scale (None = 0, Often = 1, Sometimes =2, Almost Daily = 3, Daily =4,Don’t know = 6). This tool will be used to measure the effects of the teacher training, and student ambassador components of the Peaceful Playgrounds intervention.

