### Statistical methods

Using the Statistical Package for Social Sciences (SPSS, v21), descriptive statistics and measures of central tendency will be used to describe the effect of the intervention from baseline to follow-up data in each step of the study.

Regression analysis will be completed for this study, to determine genuine relationships between the intervention, and the outcomes for physical activity levels, students’ on-task behaviour time, and frequency of social support for physical activity. Mixed-model ANCOVAs in SPSS will be computed, and each mixed model will be fitted to the data using the restricted maximum likelihood method. Percentage of occurrence (i.e. frequency) data will be analysed using ×2. For each mixed model, sex will be included as fixed effects, with the school included as a random effect to account for the effects of stepping by school. This is a standard statistical procedure for analysis of clustered datasets [27].

Intra-cluster comparisons will be completed between control and intervention periods, and for analyses involving school level characteristics of physical activity, the unit of analysis will be one scan of one area.

If schools decide to stop participating in the study, data pertaining to that school will not be included in the final analyses. Likewise, if a student selected for the behavioural observation component of the study decides to stop participating in the study their data will not be used in the final analyses. For all other components of the study (i.e., physical activity observation and Social Support), intention to treat principles will be followed and all possible data collected will be analysed.

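### The printed social-support codes do not rise with frequency and give Don't know the highest number; used as numbers, they can distort the estimated effect or reverse its sign

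*Protocol article*

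**What the plan says.** The protocol article, Social Support, describes a survey with "nine questions about how often students receive encouragement to be physically active and from who". Each answer is split by source (adult male, adult female, peers) and is "anchored to a six-point Likert scale", with the codes "None = 0, Often = 1, Sometimes =2, Almost Daily = 3, Daily =4,Don’t know = 6". Five of the labels describe a frequency. The count reaches six only if *Don't know* is included. Code 5 is not used.

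The same section gives the scale its purpose: "This tool will be used to measure the effects of the teacher training, and student ambassador components of the Peaceful Playgrounds intervention".

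Statistical methods says that "descriptive statistics and measures of central tendency will be used to describe the effect of the intervention" from baseline to follow-up. It plans regression of outcomes that include "students’ on-task behaviour time, and frequency of social support for physical activity", and continues: "Mixed-model ANCOVAs in SPSS will be computed, and each mixed model will be fitted to the data using the restricted maximum likelihood method". It also plans what appears to be a chi-square analysis for percentage-of-occurrence data. For social support, it says that "intention to treat principles will be followed and all possible data collected will be analysed". The article nowhere reorders the codes or sets *Don't know* to missing.

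**The concern.** There are two separate faults in the printed coding.

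1. **Order.** For a question about how often something happens, the code should rise with frequency. As printed it goes from *None* (0) to *Often* (1) to *Sometimes* (2), so a child who moves from *Sometimes* to *Often* loses a point.
2. **Non-answers.** *Don't know* is counted among the six points and has a number two above *Daily*. If it is averaged with the rest, a child who cannot answer contributes more than a child who is encouraged every day.

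Social support is one of the three outcome domains in the Outcomes section, and this scale is the instrument assigned to the teacher-training and student-ambassador components. The second fault matters most if the intervention changes how readily children can answer. Training that makes encouragement more visible could plausibly reduce *Don't know* answers, and with the printed codes that reduction would look like a loss of support.

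**Working it through.** The article gives no mean, effect or response distribution for this outcome, so there is no figure of its own to reproduce. The codes come from Social Support. All response shares below are assumptions.

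**Formula.** Let *v* be the mean code among children who give a frequency and *d* the share answering *Don't know*. With the printed codes the mean is M = (1 - d) × v + 6d = v + d × (6 - v).

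**Order fault alone (no Don't know).** If 20% of responses move from *Sometimes* to *Often*:
- printed codes: 0.20 × (1 - 2) = -0.20
- *Often* and *Sometimes* exchanged: 0.20 × (2 - 1) = +0.20

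For example, take shares of None 20%, Often 20%, Sometimes 40%, Almost Daily 10%, Daily 10%. The printed mean is 0 + 0.20 + 0.80 + 0.30 + 0.40 = 1.70 and falls to 1.50 after the move. With the two codes exchanged it rises from 1.50 to 1.70.

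**Don't know fault alone (no change in support).** A 10-point change in *d* moves M by 0.10 × (6 - v):

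| Assumed valid mean v | Shift in M |
|---|---|
| 1.5 | 0.45 |
| 2.0 | 0.40 |
| 2.5 | 0.35 |

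With the example shares (v = 1.70) and *Don't know* falling from 15% to 5%, M goes from 0.85 × 1.70 + 0.15 × 6 = 2.345 to 0.95 × 1.70 + 0.05 × 6 = 1.915. The change is -0.43, where the true change is zero.

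**A real gain together with fewer Don't know answers.** Let None fall from 20% to 15%, and Almost Daily and Daily each rise from 10% to 12.5%, among those who answer. The valid mean rises by 0.025 × 3 + 0.025 × 4 = 0.175, whichever way *Often* and *Sometimes* are ordered, because neither share moves. On the printed codes *v* goes from 1.70 to 1.875. If *Don't know* also falls from 15% to 5%, M goes from 2.345 to 0.95 × 1.875 + 0.05 × 6 = 2.081. A gain of about +0.18 then appears as a loss of about -0.26.

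**Stable Don't know rate.** If *d* is the same in both periods, the contrast in M is (1 - d) times the contrast in *v*. At 15% the same gain becomes 0.85 × 0.175 = 0.149. The level is too high and the effect is attenuated, but its sign is kept.

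**The case against.** The strongest reply is that the article lists response codes and not a scoring rule. It mentions no sum or mean of the items. The jump from 4 to 6 is what one would expect if 6 were a data-entry code for a non-answer, and *Often* may be a misprint for some label rarer than *Sometimes*. Scoring rules often sit in a full protocol or analysis plan that is not shown. A chi-square analysis of response percentages would not depend on the numbers at all, and a measure of central tendency need not be a mean.

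Much of this stands as a limit on the point. If *Often* is a misprint, codes 0 to 4 already rise with frequency and the order fault is editorial. The source instrument is not available here, so this cannot be settled from the text. The sentence on analysing all possible data follows rules on schools and students who stop participating; it should not be read as a decision to score non-answers.

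It does not remove the point. The article places *Don't know* inside the six-point scale and states no missing-value rule, and it plans regression on this outcome besides the chi-square analysis. A value of 6 is averaged unless someone declares it missing. A median would not be immune, since it uses the order of the codes.

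A reader might go further and infer that the trial has decided to score *Don't know* as maximum support, that the result will have the wrong sign, or that the teacher-training and ambassador components would be left with no valid measure. The article supports none of these. The first is ambiguous in the text. The second requires either a true mis-ordering or a *Don't know* rate that differs between control and intervention periods. Against the third, the playground observations also record teacher supervision and direction of activity, the Outcomes section links the social skills taught to classroom behaviour, and the Discussion asks whether training and student leadership make students more active.

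**Conclusion.** The point holds as a stated coding error with a conditional consequence. As printed, the codes are not monotone in frequency, and *Don't know* has the top value of the scale. Followed literally in the planned numerical analyses, they give a wrong score.

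The size depends on shares that the article does not report: a sign reversal of 0.20 in each direction if 20% of responses move between the two misordered labels, and 0.35 to 0.45 points for each 10-point change in the *Don't know* rate when valid answers average 1.5 to 2.5. That the printed text needs correcting is certain. Whether the trial's results would be affected is not, because that turns on the instrument's own labels and on how the data file treats code 6.

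**What to change.** Check the labels and codes against the source instrument and the data dictionary, and correct whichever is wrong so that codes 0 to 4 rise with frequency. The corrected order should come from the instrument and not be guessed from the article. State that *Don't know* (6) is declared missing for scoring, and report its rate by intervention status so that a shift in non-answers is visible. If the chi-square analysis is kept for these items, say whether *Don't know* counts as a category there.

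The cost is an edit to the coding line and slightly fewer scored items. No new data are needed if the fault lies in the article or the codes. If the labels shown to children were themselves wrong, recoding may not be enough, which is a reason to check the form before scoring.

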### Statistical methods

Using the Statistical Package for Social Sciences (SPSS, v21), descriptive statistics and measures of central tendency will be used to describe the effect of the intervention from baseline to follow-up data in each step of the study.

Regression analysis will be completed for this study, to determine genuine relationships between the intervention, and the outcomes for physical activity levels, students’ on-task behaviour time, and frequency of social support for physical activity. Mixed-model ANCOVAs in SPSS will be computed, and each mixed model will be fitted to the data using the restricted maximum likelihood method. Percentage of occurrence (i.e. frequency) data will be analysed using ×2. For each mixed model, sex will be included as fixed effects, with the school included as a random effect to account for the effects of stepping by school. This is a standard statistical procedure for analysis of clustered datasets [27].

Intra-cluster comparisons will be completed between control and intervention periods, and for analyses involving school level characteristics of physical activity, the unit of analysis will be one scan of one area.

If schools decide to stop participating in the study, data pertaining to that school will not be included in the final analyses. Likewise, if a student selected for the behavioural observation component of the study decides to stop participating in the study their data will not be used in the final analyses. For all other components of the study (i.e., physical activity observation and Social Support), intention to treat principles will be followed and all possible data collected will be analysed.

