**Methods/Design:**

Data will be collected at six New South Wales (NSW) primary schools, on physical activity levels, on-task time during classes, and social support for physical activity during a 12 month Cluster Controlled Trial (CT). Three quantitative data collection tools will be used to capture student’s physical activity levels during lunch and recess breaks (the SOPARC tool), student’s on-task behaviour during classes following recess and lunch breaks (the BOSS tool) and where students receive the most encouragement to be physically active from (the Physical Activity Social Support Scale survey). Baseline data will be analysed against follow-up data, collected after an intervention that is rolled out in all schools as part of a stepped wedge CT design.

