## Methods/Design

### Study Design

The Healthy Active Peaceful Playgrounds for Youth (HAPPY) study is a 12 month, primary school-based intervention and will be evaluated using a cluster controlled trial with a stepped wedge design. Ethics approval has been obtained from an Australian University Human Ethics Committee (HREA5201500676) as well as from the New South Wales Department of Education and Communities (SERAP2015423). The HAPPY Study is registered with the Australian and New Zealand Clinical Trials Registry (ACTRN12616000575437). Principals, teachers and parents will provide written informed consent.

Following the recruitment process, data will be collected on students’ physical activity levels during lunch and recess, students’ on-task behaviour during class following lunch, and from whom the students receive social support from to be physically active. The intervention will be rolled out in a stepped wedge design. This means that all schools will start as ‘control’ schools and that the intervention will staggered across the 12-month period of the study (three steps in total) with data will being regularly collected across the period (Fig. 1). The stepped wedge design allows for an analysis of the interventions effectiveness and efficacy. As well as having the added benefit of ensuring all schools receive the intervention [16] (i.e., playground markings and teacher training). This benefit is often absent in classic Randomised Control Trials, where control groups may receive no immediate benefit from participating in research studies. This was the main rationale behind adopting this stepped wedge design.

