### Recruitment and study participation

The HAPPY Study will be conducted in six New South Wales Department of Education and Communities (NSWDEC) schools, in the Metropolitan Sydney Region (approx. 33.51°S, 151.12°E). All eligible schools will be sent an invitation to participate by the NSWDEC Schools Sport Unit. Schools that express an interest in participating will be contacted by the research team, and will be provided with more information about the study and intervention.

To participate, schools will be required to provide school level consent for the physical activity observational data collection from the principal, and all students participating in the behavioural, and the social support data collection will be required to provide parent/guardian consent. Teachers will not need to provide consent to participate in the intervention, as no information identifying them will be recorded or reported on.

All six schools will be participate in baseline data collection during the same school term and randomisation into stepped intervention groups will take place after the baseline data.

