### Physical activity during recess and lunch

Observational data will be collected on student’s physical activity levels during lunch and recess breaks, and their utilisation of playground spaces for physical activity recorded using the System for Observing Play and Recreation in Communities (SOPARC) tool (CIAFEL, Portugal: http://activelivingresearch.org/soparc-system-observing-play-and-recreation-communities). This tool will collect student’s sex, their level of physical activity and environmental factors (i.e. time of day, temperature, recess/lunch break, presence of supervision).

SOPARC is a sampling technique in which systematic and periodic scans of individuals and environmental factors within predetermined target areas are made. Each school will have two predetermined target areas, identified by the Principal of participating schools as areas that students use frequently during recess and lunch. Following SOPARC protocols developed in a previous study [20, 21], trained researchers will complete two scans of each areas at both recess and lunch, three times during each term the study is running. The researchers are blind to the conditions of the intervention. Each school in the study will therefore be scanned 12 times each term, for a total of 288 scans across all schools during the study.

A scan involves panning from left to right, and coding each student in the area by sex (male or female), intensity of activity (Sedentary, Walking or Vigorous), and whether they are a Child, Teen, Adult or Senior. Additional data recorded for each scan will include; 1. Weather variables including temperature, rain and UV levels; 2. Time of day the observations were collected, and whether this was a lunch or recess period; 3. What type of activity the students are engaged in (i.e. handball, football, dancing, clapping games) and; 4. Teacher supervision and direction of physical activity. The SOPARC tool has been used by this research team to collect physical activity and sun-safe behaviours in primary schools, and was found to be efficient to use and had high degree of reliably, with an Intraclass Corelation Coefficient (ICC) of .912 [21].

Analysis of data collected with SOPARC will be done at an individual school level, between all schools during the same collection period and then completed on all data collected during the study.

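### The protocol states two different effect contrasts, and one of them, baseline versus follow-up, has no label for control data collected after baseline

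*Protocol article*

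**What the plan says.** The protocol article describes the comparison in two ways.

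- **Baseline versus follow-up.** The abstract (Methods/Design) says: "Baseline data will be analysed against follow-up data, collected after an intervention that is rolled out in all schools". It places this within a stepped wedge design. Statistical methods opens with descriptive statistics and measures of central tendency that "will be used to describe the effect of the intervention from baseline to follow-up data in each step of the study".
- **Control versus intervention periods.** Later in Statistical methods: "Intra-cluster comparisons will be completed between control and intervention periods". The same section plans regression and REML mixed models relating the intervention to the outcomes, with sex as a fixed effect and school as a random effect.

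The design facts that bear on this are:

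- Recruitment and study participation: "All six schools will be participate in baseline data collection during the same school term", with randomisation to step only afterwards.
- Study Design: "all schools will start as" control schools, and "the intervention will staggered across the 12-month period of the study (three steps in total").

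**The concern.** In a stepped wedge with one common baseline term, the schools in the later steps go on contributing control data after baseline. Those visits are not baseline, and they are not follow-up after an intervention. A two-label contrast has nowhere to put them, whereas control versus intervention periods does. The article does not say which contrast defines the effect.

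The randomised comparison that sets this design apart from a before-after study is between stepped and not-yet-stepped schools in the same term. It depends on exactly the visits that baseline versus follow-up leaves unlabelled. Without them, the effect is a within-school change over time that cannot be separated from season, weather, ageing of the cohort or any other calendar trend. Leaving two contrasts open also allows the choice between them to be made after the results are seen.

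**Working it through.** **Inputs**

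- Six schools: "The HAPPY Study will be conducted in six New South Wales Department of Education and Communities (NSWDEC) schools" (Recruitment and study participation).
- Three steps, all schools starting as control (Study Design).
- One common baseline term (Recruitment and study participation).
- Scan counts: "Each school in the study will therefore be scanned 12 times each term, for a total of 288 scans across all schools" (Physical activity during recess and lunch).
- Assumed, because Fig. 1 is not available here: two schools per step, and one step per term starting in the term after baseline.

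**Number of terms.** 288 / (6 × 12) = 4. Conversely, 6 × 12 × 4 = 288, so the stated total is reproduced.

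**Layout (schools in each condition)**

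| Term | Control | Intervention |
|---|---|---|
| 1 (baseline) | 6 | 0 |
| 2 | 4 | 2 |
| 3 | 2 | 4 |
| 4 | 0 | 6 |
| Total school-terms | 12 | 12 |

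The 12 control school-terms are 6 at baseline and 4 + 2 = 6 after it. At 12 scans each, that is 72 + 72 = 144 control scans.

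**Reading A: baseline versus post-intervention follow-up.** This uses 6 + 12 = 18 of the 24 school-terms. It drops 6 / 12 = 50% of the control school-terms. These include all those in terms 2 and 3, the only terms with both conditions present.

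On these 18 cells the intervention indicator is 1 in every term except baseline, so it equals the sum of the indicators for terms 2, 3 and 4. A design matrix with 6 school, 3 term and 1 intervention columns has rank 9 of 10. No term-adjusted effect can be estimated. Making school a random effect does not help, because the aliasing is between intervention and term. On all 24 cells the same matrix has rank 10 of 10.

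**Sensitivity to schools per step.** With n₁, n₂, n₃ schools in the three steps, the post-baseline control school-terms number n₂ + 2n₃.

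- (4, 1, 1): 1 + 2 = 3, a loss of 3 / (6 + 3) = 33%.
- (1, 1, 4): 1 + 8 = 9, a loss of 9 / (6 + 9) = 60%.

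The aliasing holds for any such split, provided the first step comes after the baseline term.

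**Reading B: baseline versus everything later.** Of 18 post-baseline school-terms, 6 are untreated. The treated share within school averages (1 + 1 + 2/3 + 2/3 + 1/3 + 1/3) / 6 = 0.67, so a constant effect would be recovered at two thirds of its size.

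**Bias from a linear calendar trend of one unit per term (least squares with school effects)**

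| Data and model | Trend bias | Share of a constant effect recovered |
|---|---|---|
| Reading A, no term | 2.44 | 1.00 |
| Reading B, no term | 2.00 | 0.67 |
| Control versus intervention, all data, no term | 2.00 | 1.00 |
| Control versus intervention, all data, with term | 0 | 1.00 |

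For the first row, the within-school differences in mean term number are 2, 2.5 and 3 for steps 1, 2 and 3, with weights 3/4, 2/3 and 1/2. The result is (1.5 + 1.667 + 1.5) / 1.917 = 2.44.

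The third row shows that relabelling the contrast restores the lost data but not the concurrent comparison. That needs term in the model as well.

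**The case against.** A reader might infer that the trial's effect analysis will throw away half its control data. The document does not support that.

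- The sentence in Statistical methods concerns descriptive statistics only. The inferential analysis is described separately, as mixed models and a comparison of control with intervention periods. Under Study Design, a not-yet-stepped school-term is a control period, so it has a place there.
- For physical activity and social support, the section commits to analysing all the data that can be collected. Nothing in the article excludes or recodes the later control terms.
- The abstract sentence is a one-line summary set within a stepped wedge design. It describes follow-up as coming after the intervention, which counts against Reading B and its two-thirds figure.
- The phrase about each step may mean before versus after each group's own crossover.
- The section on physical activity during breaks foresees an analysis across all schools in the same collection period.

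Most of this stands, and it makes the loss conditional. It does not remove the conflict. The abstract's statement is not limited to description, and the descriptive sentence still calls a before-after change the intervention's effect. Analysing all data does not settle whether a not-yet-stepped visit counts as control, and that commitment does not extend to the behaviour outcome. The same-period analysis covers one outcome of three and does not say that schools are compared by stepped status. Even before versus after each group's own crossover is a within-school change mixed with calendar time. The Discussion says only that time can serve as a variable, and the one covariate named for the mixed models is sex.

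**Conclusion.** The point holds as an inconsistency: the article gives two contrasts for the effect, and they do not use the same data. It is worth correcting because following the abstract literally would give a before-after change confounded with term.

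The size is conditional. If baseline versus post-intervention follow-up were used for estimation, 6 of 12 control school-terms (33% to 60% under uneven splits) and every concurrent control would be left out, and intervention would be fully aliased with term. This rests on four terms, which follow from the stated scan counts, and on the assumed step layout. It is not established that the mixed models or the control-period comparison lose these data. The two-thirds dilution rests on a reading that the abstract's own wording disfavours, so it should not be presented as a consequence of the plan.

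**What to change.** In the abstract and in Statistical methods:

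1. Define exposure for each school-term by the randomised step.
2. State that every visit to a school that has not yet stepped, including visits after baseline, is control data in every effect estimate, for all three outcomes.
3. Estimate the effect from all school-terms, with school term as a fixed effect alongside the school random effect.
4. Label the step-wise baseline-to-follow-up summaries as descriptive change, not as the intervention effect.

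Item 3 is needed because items 1 and 2 alone leave the trend bias in place.

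**Cost.** No extra data collection is required; the change is to wording and to one model term. The before-after change can no longer be reported as the effect, and the term-adjusted estimate will be somewhat less precise.

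### Sex is a fixed effect in every mixed model, but a playground scan has no single sex value; keeping sex as a factor needs rows below the scan, which the stated model treats as independent within school

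*Protocol article*

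**What the plan says.** All of this comes from the protocol article.

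- **Statistical methods, models.** Physical activity levels, on-task behaviour and social support are all named as regression outcomes. Mixed-model ANCOVAs follow: "each mixed model will be fitted to the data using the restricted maximum likelihood method". The covariate and the random effect are then set for all of them: "For each mixed model, sex will be included as fixed effects, with the school included as a random effect". No other random effect and no residual covariance is named.
- **Statistical methods, unit.** The next paragraph says: "for analyses involving school level characteristics of physical activity, the unit of analysis will be one scan of one area". The opening words limit this rule to school-level analyses of physical activity.
- **Physical activity during recess and lunch.** A scan is made by "coding each student in the area by sex (male or female), intensity of activity (Sedentary, Walking or Vigorous", among other codes. Sex is therefore recorded for each child inside a scan.
- **Scan schedule, same section.** Each school is to be "scanned 12 times each term, for a total of 288 scans across all schools during the study".

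**The concern.** A scan of a playground area holds boys and girls at once, so a record whose unit is the scan has no sex value. Sex cannot enter such a record as a factor. To obey the sex rule, the analyst has to go below the scan, to a boys' row and a girls' row or to one row per coded child. That departs from the stated unit.

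Rows from one scan share the time, the area, the weather and the supervision, and they always have the same intervention status. With school as the only random effect, the model takes them to be independent once school is allowed for. If they are in fact positively correlated, the second row of a scan adds less information about the intervention than the model credits, and the p-value for the intervention effect is too small.

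Playground activity is the outcome by which the Outcomes section judges the playground markings, and the sample size section is written for the physical activity observations. The row structure of this model is therefore worth fixing before data are seen.

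**Working it through.** **The plan's own figure.** The scan total reproduces if the schedule means one recess and one lunch scan of each area per visit: 2 areas × 2 scans × 3 visits = 12 per school-term, and 12 × 6 schools × 4 terms = 288. Four terms is what 288/(6 × 12) implies. Reading the schedule as two scans at each break gives 24 per school-term and 24 × 6 × 4 = 576. The result below does not depend on which is meant.

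**Assumptions, none given by the article.** Two-sided nominal alpha of 0.05. A boys' row and a girls' row per scan with equal variance σ². Correlation ρ between the two rows of a scan, after allowing for school.

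**Two rows per scan.** Both rows have the same intervention status, so the intervention contrast depends on their sum.

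- Variance of the sum as the model assumes: 2σ².
- True variance of the sum: 2σ²(1 + ρ).
- Model standard error divided by the correct one: 1/√(1 + ρ).
- True type I error: 2[1 − Φ(1.96/√(1 + ρ))].

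| ρ (assumed) | SE ratio | Type I, formula | Type I, simulated, two rows |
|---|---|---|---|
| −0.3 | 1.195 | 1.9% | 2.0% |
| 0 | 1.000 | 5.0% | 6.1% |
| 0.2 | 0.913 | 7.4% | 7.5% |
| 0.5 | 0.816 | 11.0% | 10.6% |
| 0.8 | 0.745 | 14.4% | 15.1% |

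The simulation used 6 schools, 4 terms, 12 scans per school-term, two schools crossing over per step (assumed), a school random intercept fitted by REML, a sex fixed effect, independent scans and 3000 replicates. One row per scan without sex gave 4.5% to 5.7% across the same values of ρ. At ρ = 0 both layouts were slightly above nominal (6.1% and 5.7%), so little of that excess is due to splitting scans.

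A second simulation (4000 runs, school and term as fixed effects) gave 11.0% with 12 scans per school-term and 11.1% with 24 at ρ = 0.5. The scan count does not drive the result.

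**One row per child.** With c children per scan and within-scan intraclass correlation r, the design effect 1 + (c − 1)r replaces 1 + ρ. The range is wide:

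- c = 10, r = 0.02: 1 + 9 × 0.02 = 1.18, type I error 7%.
- c = 20, r = 0.05: 1 + 19 × 0.05 = 1.95, type I error 16%.
- c = 30, r = 0.2: 1 + 29 × 0.2 = 6.8, type I error 45%.

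For the same data, child rows are worse than two rows. Take c = 20 split evenly into 10 boys and 10 girls, with r = 0.05. The correlation between the boys' and girls' means is 10 × 0.05/(1 + 9 × 0.05) = 0.5/1.45 = 0.345. The two-row factor is then 1.345 (type I error 2[1 − Φ(1.96/√1.345)] = 9.1%), against 1.95 for child rows.

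**The case against.** - **Nothing in the article says scans will be split.** This is correct. A split is an inference, and it would itself break the rule that the scan is the unit. A reader might infer that the planned analysis is known to give p-values that are too small; the article does not support that. It supports only that the two rules conflict, and that one way of resolving the conflict has this consequence.
- **The scan unit is limited to school-level analyses, so the sex rule may be meant for other models.** The qualifier is real and its reach is unclear. But the sex rule covers each mixed model and follows directly after physical activity is listed as a regression outcome. If other SOPARC models do use sex, their rows lie below the scan and still have no within-scan term.
- **The share of boys in a scan could be a covariate, or the models could be run separately by sex.** Either would avoid duplicated rows, and the inflation would not arise. Neither is described, and neither is sex as a fixed effect. They are acceptable repairs, not what the text now says.
- **The direction is conditional.** This stands. Shared conditions make a positive correlation plausible, but boys and girls competing for space could make it negative, and the article gives no value.
- **A journal article leaves row layout to a fuller plan.** Silence on layout alone would be no finding. Here the covariate, the random effect and the unit are all stated, and they do not agree. Whether a fuller plan adds a scan term cannot be seen.
- **Tests of sex differences would lose power.** A reader might infer this as a further harm. The article states no sex hypothesis and no sex-by-intervention term, so no planned result is affected.

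**Conclusion.** The point holds as an unreconciled specification with a conditional consequence. For the SOPARC outcome, sex as a fixed effect in every mixed model and the scan as unit do not fit together, and no term for dependence within a scan is named.

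If the conflict is resolved with boys' and girls' rows under a school random effect only, type I error for the intervention effect is about 7% to 14% for assumed correlations of 0.2 to 0.8. It is 5% at zero and below 5% at negative values. Child rows would be worse for the same within-scan correlation. If one row per scan is used, this particular error does not arise.

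These figures rest on an assumed alpha of 0.05, equal row variances, assumed correlations, and scans that are independent of each other apart from school.

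**What to change.** State the row structure of the SOPARC model for the intervention effect as one of two consistent options:

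- **(a)** One row per scan with both sexes combined and no sex factor. The share of boys may be a covariate if wanted. Report boys' and girls' results separately.
- **(b)** One boys' row and one girls' row per scan, with sex as a within-scan factor and a within-scan covariance in addition to the school random effect. This can be a scan random intercept or an unstructured 2 × 2 residual covariance. The unstructured form also allows a negative correlation, which a random intercept cannot represent.

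Limit sex as a plain fixed effect to the student-level models for BOSS and Social Support.

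The cost is about two sentences of analysis text and at most one extra model term, with no new data. The interval for the intervention effect may be wider. The change removes dependence within a scan only. Correlation between repeated scans of the same areas is a separate matter that it does not address.
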